### Data collection methods

2.8

**Participant**
**i****nterview**: At baseline and follow-up, trained RA will collect in-person data, using interviewer-administered surveys and objective measurements on Android tablet with the REDCap electronic data collection platform. The data collection will include (a) Sociodemographic data including age, gender, marital status, level of education, occupation using pre-tested standard questionnaire; (b) Lifestyle behaviors including fruit and vegetable intake using the diet quality questionnaire [32], physical activity using the global physical activity questionnaire [33], alcohol consumption, tobacco use, knowledge of hypertension [34], salt intake, and adherence to prescribed medication [35]; (c) Quality of life through EQ-5D-5L questionnaire.

**Anthropometric measurement:** We will measure weight using a calibrated digital weighing scale wth participants in light clothing, and height barefoot against a wall using a measuring tape scaled in centimeters.

**Blood pressure measurement:** Trained RA will measure blood pressure using a calibrated OMRON-16 digital instrument three times between intervals of at least 5 min with the participant sitting with back supported, feet flat, and arm supported at heart level [36]. The average of the three measurements will be used for analysis.

**Healthcare providers interview:** Trained RA will interview healthcare providers in 102 health facilities to assess the current HTN control efforts, including guidelines, equipment, facilities, human resources, and medicine availability, using a semi-structured pre-tested questionnaire.

**Process tracking:** The process tracking system will serve as a monitoring tool for program implementation and maintenance. FCHVs will record of group meetings and home visits, including schedules, BP readings, medication adherence, and referrals. During monthly health facility meetings, the facility in-charge will document agenda, challenges, and solutions. Research staff will attend monthly meetings and will also contact FCHVs either in person or by phone, and maintain field notes on observations related to the implementation process [37].

**Periodic reflection interviews:** We will conduct periodic reflections (PRs) with FCHVs and healthcare workers from intervention health facilities to capture evolving experiences, contextual changes, and adaptations [38]. We will purposively select 12- 24 health facilities (1 - 2 health facilities per municipality) to ensure a diversity by geography, community demographics, health facility characteristics, and patient volumes. One heathworker per selected facility and two FCHVs per facility will participate in 30-min interviews conducted every 2 to 3 months in conversational Nepali. PRs will explore implementation activities, alignment with routine work, barriers, facilitators, and stakeholder responses. Interviews will be iterative, allowing exploration of how barriers and facilitators change over time.

**Meeting observations:** We will observe monthly health facility meetings in selected intervention facilities, selected HTN group meetings, and home visits by FCHVs every two to three months. Observations will include diverse settings and participant characteristics. These observations will focus on understanding how the intervention is integrated into routine health facility activities, meeting dynamics, participation, and communication between healthcare workers and FCHVs. Meeting observations will be guided by a checklist. Data gathered will be recorded in the form of field notes.

**Focus group discussions (FGDs):** We will conduct 6-9 FGDs with purposefully selected FCHVs in intervention sites post-implementation and post-maintenance to capture diverse experiences. FCHVs will represent varied experience, proximity to health facilities, need for peer support, literacy levels, communication styles, and caste or religion. The FGDs will be conducted in Nepali in a private accessible setting. The discussion guide will build on rapid analysis of PR to explore barriers and facilitators, and the strategies to strengthen intervention implementation and maintenance.

**Key informant interviews (KIIs):** We will conduct KIIs with 12-16 key informants from federal and provincial MoH and municipal officials at two time points: post-implementation and post-maintenance to explore support for the program, barriers and facilitators, and leadership perspectives. Participants will be purposively selected for diverse insights. Interviews will assess integration of CHPC into government systems and progress toward sustainability, with iterative questioning to explore emerging themes.

#### Power and sample size

2.8.1

The primary aim is to assess whether the implementation model meets acceptable rates, i.e. 80% of adoption, implementation, reach, and maintenance of the CHW-delivered HTN care**.** All 51 intervention health facilities will be included, providing 4.2% precision with a cluster size of 9 CHW per health facility and an intraclass correlation coefficient 0.04 [39]. To assess the clinical outcome, 3572 patients, 35 per clusters across 102 clusters will be enrolled. Assuming standard deviation at 17.75 mmHg for HTN [18], and intra-cluster coefficient (ICC) of 0.015 [40], with 10% loss to follow-up, the study has 90% power to detect a 3 mmHg systolic BP (primary clinical outcome) in a subsample of participants with uncontrolled hypertension, approximately 60% of the total. These calculations were computed using PASS 2024, version 24.0.2.8 [41].

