### Outcomes

2.7

Following the Hybrid Type III effectiveness-implementation appraoch, this study assesses both implementation and clinical outcomes (Table 2). The primary implementation: Reach, Adoption, Implementation, and Maintenance [20] in intervention arm, measured at health facility level. The clinical outcome is the mean change in systolic blood pressure (SBP) between intervention and control arms from baseline to 12 months, measured at the participant level. Secondary clinical outcomes diastolic BP, control, awareness of HTN diagnosis, lifestyle practices, medication adherence, quality of life, and economic costs compared between intervention and control groups.

**Table 2 tbl2:** Study outcomes.

Implementation Outcomes			
		**Measures**	**Data Sources**
Reach	Percentage of FCHVs implementing the program participating in at least 8 of the 12 monthly meetings	At least 80% of the trained FCHVs will participate in at least 8 of the 12 monthly meetings;	Process tracking data, including the number of FCHVs participating in each group session meeting and themes discussed, as reported by the health facility in charge. Attendance records will be collected by study staff during monthly process tracking calls with the health facility in charge.
	Percentage of patients with hypertension in the community aware of their high BP status	At least 80% of the patients with hypertension in the community are aware of their diagnosis.	Participant survey
Effectiveness	Systolic BP (mmHg)	The net difference in mean systolic BP (mmHg) will be measured after 12 months between the intervention and control groups.	Baseline and end-line surveys
Adoption	Percentage of the health facilities intending to adopt the program.	Adoption will be a dichotomous measure (adopted vs not adopted). Adoption is defined as health facilities where FCHVs complete the initial FCHV training sessions	Process tracking data, FCHVs attending the training, based on attendance logs

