Implementation	Percentage of the health facilities implementing the minimum standard of program implementation.	At least 80% of the health facilities will implement a minimum standard for program implementation. Implementation will be a dichotomous measure (successful vs inadequate). A health facility will be defined as having successfully implemented the program if: (1) health facility in charge conducts monthly coaching and technical support at least 8 out of 12 months in a year; (2) 80% of FCHVs conduct first home visits to at least the 80% of the target clients; (3) 80% of FCHVs conduct at least one group meeting with at least 80% of the target clients; and, (4) 80% of FCHVs submit monthly reports at least 8 out of 12 months in an implementation year. As secondary outcomes, we will also: ● assess the extent to which each core component was implemented and ● report the percentage of health facilities implementing all core components. ● explore facilitators and barriers to implementation.	Healthcare worker survey, Process tracking data: including a monthly checklist documenting intervention component completed, and HTN patients' participation in them, to be collected by the health facility in charge during standing monthly meetings with FCHVs. Meeting observations and periodic reflection interviews will be used to explore fidelity and the facilitators and barriers.

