### Analysis plan

2.9

**Reach, Adoption, Implementation, and Maintenance:** We will assess adoption, implementation, reach and maintenance (Table 2) by calculating the proportion of facilities that achieve each component and all program components, with 95% confidence interval. Qualitative data from PRs, observations, KIIs and FGDs will be triangulated. PRs and observation-based data will be analzed using CFIR-based deductive rapid analysis [42] to identify barriers, facilitators, and the fidelity of the CHPC intervention at FCHV and health facility level. The primary analyst will document detailed notes, summarizing findings in matrices, and a secondary analyst will review recordings to refine the analysis. We will analyze FGDs and KIIs abductive analysis [43], using CFIR in NVivo 12.0.

**Clinical Effectiveness**: We will analyze the primary outcome, mean systolic BP at 12 months using intention-to-treat approach, with generalized estimation equation (GEE) with the identity link, exchangeable working correlation, and robust variance. If a substantial baseline imbalance occurs, we will conduct adjusted sensitivity analysis adjusted for age, marital status, education to assess the robustness of the primary analysis. We will also use ANCOVA for clustered data to conduct difference-in-difference analysis most efficiently [44]. In ‘per protocol’ analysis, we will exclude participant with fewer than 2 visits, no follow-up assessment, or post-randomization ineligibility. Causal inference probability weighting methods will also adjust for non-adherence to the protocol [45]. Secondary outcomes will also be analyzed using GEE with the identity link (for continuous variables) and the log link for binary variables with exchangeable correlation and robust variance. We will conduct stratified analyses to examine treatment effects by rural and urban areas, blood pressure control status at baseline, and biological sex.

**Costing:** We will calculate total implementation and maintenance costs by summing all components. We will examine associations between costs and key factors such urban/rural location, health facility catchment area, and FCHV-to-participant ratio using bivariate and multivariable analysis. We will also conduct budget impact analysis for assess the financial consequences of scaling the intervention at municipal level.

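### The 4.2% precision applies to a proportion of FCHVs; adoption, implementation and maintenance are scored on 51 facilities, where the half-width at 80% is about 11 points

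*Protocol article*

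**What the plan says.** Section 2.8.1 (Power and sample size) names the benchmark for the primary aim as "80% of adoption, implementation, reach, and maintenance of the CHW-delivered HTN care". The sample for this aim is every facility in the intervention arm, 51 in all, and the article describes that sample as "providing 4.2% precision with a cluster size of 9 CHW per health facility and an intraclass correlation coefficient 0.04". No outcome is excepted, and no other precision is given for the implementation outcomes.

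Other sections fix the unit of these outcomes:

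- Section 2.7, text: the primary implementation outcomes are assessed "in intervention arm, measured at health facility level".
- Table 2, Adoption: a dichotomous measure. "Adoption is defined as health facilities where FCHVs complete the initial FCHV training sessions".
- Table 2, Implementation: "At least 80% of the health facilities will implement a minimum standard for program implementation". Each facility is classed as either successful or inadequate. Maintenance uses the same structure in the maintenance year.
- Table 2, Reach: "At least 80% of the trained FCHVs will participate in at least 8 of the 12 monthly meetings". A second Reach measure is the percentage of patients with hypertension who know their diagnosis.
- Section 2.9 (Analysis plan): all four outcomes are assessed by "calculating the proportion of facilities that achieve each component and all program components, with 95% confidence interval".

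**The concern.** A cluster size and an ICC enter the precision of a proportion only when several members of each cluster are counted. If every facility contributes one yes/no result, there are 51 observations and nothing is clustered within them. A precision built on nine volunteers per facility therefore cannot describe adoption, implementation or maintenance as Table 2 defines them.

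These are three of the four primary outcomes of a hybrid type III trial, and the stated aim is to judge them against 80%. A reader told ±4.2 points would take an observed 80% to mean a true rate between roughly 76% and 84%. If the real interval is much wider, an observed result near the benchmark says far less about whether the benchmark has been met.

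Reach has the converse problem. Table 2 defines it in percentages of volunteers and of patients, while section 2.9 would estimate a percentage of facilities. Table 2 gives no rule for scoring a facility as having met Reach.

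**Working it through.** **Inputs.** Target proportion p = 0.80, k = 51 facilities, m = 9 volunteers per facility and ICC = 0.04 (all section 2.8.1). The 95% confidence level is from section 2.9. The unit of each outcome is from section 2.7 and Table 2.

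**1. Reproducing the stated figure at volunteer level**

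- Volunteers: 51 × 9 = 459
- Design effect: 1 + (9 − 1) × 0.04 = 1.32
- Effective sample size: 459 / 1.32 = 347.7
- Half-width: 1.96 × √(0.80 × 0.20 × 1.32 / 459) = 0.0420, or 4.2 points

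This matches the article. Nearby alternatives do not: 3.7 points without the design effect, 5.3 points at p = 0.50, and 3.5 points with a 90% interval. The match identifies the volunteer as the unit.

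**2. The same calculation at facility level**

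- Half-width: 1.96 × √(0.80 × 0.20 / 51) = 0.110, or 11.0 points
- Ratio to the stated value: 11.0 / 4.2 = 2.6
- Facilities needed for ±4.2 points: 1.96² × 0.16 / 0.042² = 348.4, so 349

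The smallest count that reaches 80% is 41/51 (80.4%). Its 95% interval is 66.9% to 90.2% (Clopper-Pearson) or 67.5% to 89.0% (Wilson).

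**3. Sensitivity**

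| Assumption | Half-width |
|---|---|
| 51 facilities, p = 0.80 | 11.0 points |
| As above, treated as 51 sampled from 102: × √(51/101) | 7.8 points |
| 51 facilities, p = 0.90 | 8.2 points |
| 51 facilities, p = 0.95 | 6.0 points |

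All exceed 4.2 points. The simple formula gives 4.2 only when the rate is near 97.5% (4.3 points at 97.5%, 4.1 at 97.7%).

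**4. What this means for an 80% benchmark**

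The article does not say how the benchmark is judged, so two readings are shown, with binomial probabilities for 51 facilities.

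- *Point estimate of at least 80% (41/51 or more).* A true rate of 75% passes with probability 0.24 and a true rate of 80% with probability 0.56.
- *Lower exact 95% limit above 80%.* At 46/51 the limit is 78.6% and at 47/51 it is 81.1%, so 47/51 (92%) is needed. A true rate of 90% passes with probability 0.41.

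**5. Matching units across the sections**

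| Outcome | Unit in Table 2 | Unit behind 4.2% | Unit in section 2.9 |
|---|---|---|---|
| Adoption | Facility | Volunteer | Facility |
| Implementation | Facility | Volunteer | Facility |
| Maintenance | Facility | Volunteer | Facility |
| Reach, meeting attendance | Volunteer | Volunteer | Facility |
| Reach, awareness | Patient | Volunteer | Facility |

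The stated precision fits the definition of one Reach measure and, as section 2.9 is written, none of the planned analyses.

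**The case against.** The strongest reply is that the figure drives nothing. All intervention facilities are included, so the number is fixed by the district. Section 2.9 already plans a facility-level proportion with a confidence interval, so the reported intervals for adoption, implementation and maintenance should be right whatever section 2.8.1 says. That limits the harm to the planning claim. It does not make the printed figure correct, and it is the only precision offered for the primary aim.

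It can also be said that ±11 points assumes the 51 facilities stand for a wider population, and that it holds only near 80%. Both are true. The finite-population version, 7.8 points, is 1.9 times the stated value rather than 2.6 times. But the article plans confidence intervals, uses an ICC and invokes no such correction, and 80% is its own benchmark.

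The article never promises a lower confidence limit above 80%; the wording of Table 2 reads more naturally as a point-estimate target. That stands, so the 47/51 figure illustrates one reading and is not a rule the authors adopted. The formal decision rule and the type of interval may properly sit in the SAP.

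On Reach, the text of section 2.7 also speaks of facility level, so facilities might be meant to be scored on Reach. But Table 2 contains only volunteer and patient percentages, so the sections still need reconciling.

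Finally, several criteria for Implementation and Maintenance are built on volunteer percentages, so a volunteer-level precision could also serve descriptive summaries of those components. That is fair, but in the primary outcome they collapse to a single result per facility.

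**Conclusion.** The point holds. The arithmetic behind 4.2% is correct, but it is attached to outcomes with a different unit. For adoption, implementation and maintenance the 95% half-width at 80% is about 11 points, and 7.8 points under a finite-population argument that the article does not make. This rests on one binary result per facility, all 51 facilities contributing, and independence between facilities. The half-width narrows at higher rates, but stays above 4.2 points at 90% and at 95%. The Reach mismatch between Table 2 and section 2.9 is a secondary contradiction within the same set of outcomes. The figure should be corrected because the primary aim relies on it.

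**What to change.** In section 2.8.1, state that the 4.2% applies to proportions of FCHVs, namely the meeting-attendance measure of Reach. Add that for adoption, implementation and maintenance, with 51 facilities, the 95% half-width at 80% is about 11 points (exact interval about 67% to 90% at 41/51).

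In section 2.9, reconcile Reach with Table 2. Either analyse attendance at FCHV level and awareness at patient level, with intervals that allow for clustering by facility, or add to Table 2 a rule that scores each facility on Reach.

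It would also help to say, here or in the SAP, whether meeting 80% refers to the point estimate (41/51 or more) or to the lower exact 95% limit (47/51 or more), and to use exact or Wilson intervals for the facility-level outcomes.

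The cost is wording and a less favourable stated precision. No extra facilities, participants or data are needed, and the article's trial status section says that no outcome data have been accessed, so the change can be made before any results are known.

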### Analysis plan

2.9

**Reach, Adoption, Implementation, and Maintenance:** We will assess adoption, implementation, reach and maintenance (Table 2) by calculating the proportion of facilities that achieve each component and all program components, with 95% confidence interval. Qualitative data from PRs, observations, KIIs and FGDs will be triangulated. PRs and observation-based data will be analzed using CFIR-based deductive rapid analysis [42] to identify barriers, facilitators, and the fidelity of the CHPC intervention at FCHV and health facility level. The primary analyst will document detailed notes, summarizing findings in matrices, and a secondary analyst will review recordings to refine the analysis. We will analyze FGDs and KIIs abductive analysis [43], using CFIR in NVivo 12.0.

**Clinical Effectiveness**: We will analyze the primary outcome, mean systolic BP at 12 months using intention-to-treat approach, with generalized estimation equation (GEE) with the identity link, exchangeable working correlation, and robust variance. If a substantial baseline imbalance occurs, we will conduct adjusted sensitivity analysis adjusted for age, marital status, education to assess the robustness of the primary analysis. We will also use ANCOVA for clustered data to conduct difference-in-difference analysis most efficiently [44]. In ‘per protocol’ analysis, we will exclude participant with fewer than 2 visits, no follow-up assessment, or post-randomization ineligibility. Causal inference probability weighting methods will also adjust for non-adherence to the protocol [45]. Secondary outcomes will also be analyzed using GEE with the identity link (for continuous variables) and the log link for binary variables with exchangeable correlation and robust variance. We will conduct stratified analyses to examine treatment effects by rural and urban areas, blood pressure control status at baseline, and biological sex.

**Costing:** We will calculate total implementation and maintenance costs by summing all components. We will examine associations between costs and key factors such urban/rural location, health facility catchment area, and FCHV-to-participant ratio using bivariate and multivariable analysis. We will also conduct budget impact analysis for assess the financial consequences of scaling the intervention at municipal level.

**Cost-effectiveness:** We will estimate incremental cost-effectiveness ratios (ICERs) per BP-controlled participant and per quality-adjusted life-year (QALY) gained based on WHO threshold for Nepal [46]. Economic evaluation will be done from the health system perspective with a discount rate of 3.5% [47]. We will conduct probabilistic and deterministic sensitivity analysis to test the robustness and assess the best- and worst-case scenarios, following Gold Commission guidelines [48] and the Bill & Melinda Gates Foundation [49].

**Equity:** We will collect patient survey data on out-of-pocket (OOP) costs and compare the OOP costs between CHPC participants and those the usual care. This will allow assessment of us to equity, by examining financial risk protection and differences in OPP costs across care models. Using extended cost-effectiveness method (ECEM) [50], we will assess distributional impacts by gender, ethnicity, and socio-economic status. The ECEA will estimate catastrophic health expenditure [51,52], defined as medically expenditure exceeding 10% of household income, using OOP cost survey data [53].

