### Study design

2.1

We will evaluate primarily Reach, Effectiveness, Adoption, Implementation and Maintenance (RE-AIM) framework [20] implementation outcomes and secondarily assess effectiveness outcomes. Primary implementation outcomes wil be measured in the intervention group. We will conduct a non-blinded two-arm cluster-randomized trial to assess the effectiveness of the intervention on mean systolic BP compared to the control group at 12 months. The health facility will be randomly assigned to the intervention or control group. The intervention arm will receive the community health worker (CHW) intervention and strategies, while the control arm will receive the standard of care.

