**Table 1 tbl1:** Implementation strategies’ core and adaptive components.

	Core components	Adaptive components
**Leadership support and ongoing program promotion**	Health Coordinators from the Provincial MoH will participate in the planning, execution and monitoring of the study. In provincial MoH health review meetings, hypertension-related indicators (proportion of population screened, HTN detected, HTN under medication, HTN control) will be discussed using the government's health management information system data.	Health coordinators will be encouraged to discuss how to engage patients and health workers in planning and monitoring CHPC. In review meetings, tip sheets will be provided listing the contextual challenges and possible solutions in achieving HTN screening, detection, medication, and control.
**Capacity building**	Healthcare workers training; FCHV training; Coaching and technical support from healthcare workers to FCHV in a monthly meeting	Health care workers can connect with the research staff on the telephone when needed; FCHVs can connect with healthcare workers on the phone when needed; FCHVs may be provided with the list and contact details of referral centers and related physicians to smoothen referral of patients with high BP
**FCHV Home visit and group meeting**	1st visit: introduction, rapport building, goal setting, BP monitoring; 2nd- 4th visit: BP monitoring, action and reflection, discussing problems faced in achieving their goals and implementing their action plans	Additional visits/meetings can be scheduled depending on patients' needs and FCHV's availability. May include family members who are decision makers during home visit session; May conduct the home visit session in groups living in the same household
**Social network**	Monthly meetings of health care workers in the municipality are held. Monthly meeting of FCHVs in the health facility.	May conduct experience sharing regarding the CHPC in meetings conducted for other purposes; May invite community leaders or patient representatives to the meetings

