**Coaching and technical assistance**: We will provide ongoing support for FCHVs by training the healthcare workers to coach and supervise them. Research team members will attend the monthly meeting, offer phone support, and provide technical assistance. Healthcare workers will use monthly meetings and phone communication to support FCHVs. Furthermore, we will also connect intervention health facilities to the telemonitoring services of Dhulikhel hospital to support HTN case management and referrals, when needed.c.**FCHV group meetings and home visits:** After completing training and competency assessment, FCHVs will conduct group meetings and home visits. From the list of patients with HTN enrolled at screening, FCHVs will form HTN patient group and organize four sessions in a year. They will first invite HTN patients to attend group meetings, those with uncontrolled HTN, adherence challenges, or inability to attend will receive home visits. In the first visit (∼ 90 min), FCHVs will explain the purpose, monitor blood pressure, discuss HTN and its consequences, and provide education using flip chart. Participants will choose lifestyle goals including physical activity, healthy diet, tobacco and harmful use of alcohol, attending medical follow-up, BP monitoring, and antihypertensive medication use. In subsequent sessions (∼ 60 min), the FCHVs will measure BP, review progress, address challenges, and update action plans with participants and their family members.d.**Social network:** Using learning networks concept [29], we will facilitate information exchanges among healthcare workers and FCHVs to support shared problem-solving, learning and program implementation [30,31]. These exchanges will occur during regular municipal and health facility meetings. We will provide discussion questions, with healthworkers facilitating discussions.

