### Strength and limitations

3.1

The primary strength of this study lies in its Hybrid Type III cluster-randomized design, which simultaneously evaluates clinical effectiveness and the real-world implementation process. By utilizing the health facility as the unit of randomization, the trial aligns with Nepal's existing primary healthcare infrastructure, increasing the potential for institutionalization and scalability. The use of a mixed-methods approach, guided by the RE-AIM and CFIR frameworks, provides a comprehensive understanding of implementation fidelity and contextual barriers. Furthermore, the inclusion of an Extended Cost-Effectiveness Analysis (ECEA) ensures that the findings offer actionable data for policymakers regarding the reduction of catastrophic health expenditures for rural populations.

However, the study has certain limitations. First, the trial uses non-blinded design due to then ature of the intervention, which may introduce performance bias among healthcare workers and participants. Second, implementation outcomes may vary across municipalities because of differences in capacity, geographic accesibility and community engagement. Third, although intervention is integrated within existing health systems, variations in FCHV motivation and local leadership support may incidence program fidelity and sustainability. Fourth, while the risk of cross-cluster contamination was formally assessed and mitigated through geographic buffering and restricted training, some spillover may occur during municipal-level administrative meetings. We will monitor this through qualitative probes in our periodic reflections and address it via a secondary per-protocol analysis if significant. Finally, the reliance on self-reported data for lifestyle behaviors may introduce social desirability bias.

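### The two-visit per-protocol exclusion has no control-arm counterpart, and that analysis cannot address spillover as promised

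*Protocol article*

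**What the plan says.** Section 2.9 (Analysis plan, Clinical Effectiveness) makes intention-to-treat the primary approach for SBP at 12 months. It then defines a per-protocol set: "we will exclude participant with fewer than 2 visits, no follow-up assessment, or post-randomization ineligibility". No separate rule is given for controls. The next sentence adds probability weighting for non-adherence, as a further method and not as a replacement.

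What a visit is has to be read from section 2.6. Under FCHV home visits and group meetings, Table 1 lists "1st visit: introduction, rapport building, goal setting, BP monitoring; 2nd- 4th visit: BP monitoring, action and reflection". The text there has FCHVs invite patients to group sessions, while "those with uncontrolled HTN, adherence challenges, or inability to attend will receive home visits". Section 2.1 describes the comparator: the intervention arm gets the community health worker programme, "while the control arm will receive the standard of care".

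Section 3.1 (Strength and limitations) says that contamination was "mitigated through geographic buffering and restricted training", concedes that some spillover may arise at municipal administrative meetings, and says the team will monitor it through probes in the periodic reflections and "address it via a secondary per-protocol analysis if significant". Section 2.6 also describes the social-network strategy: "Monthly meetings of health care workers in the municipality are held" (Table 1) and "These exchanges will occur during regular municipal and health facility meetings" (item d).

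**The concern.** A per-protocol set keeps some link to the randomized comparison only if its exclusions work alike in both arms. Here one of the three cannot. Trimming one arm by attendance compares intervention participants who chose, or were able, to attend with all controls, including those who would not have attended had they been offered sessions. Any prognostic difference between attenders and non-attenders then goes straight into the estimate.

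The second problem is a mismatch between two sections. Spillover means that control participants or facilities receive part of the intervention. Removing low attenders from the intervention arm does nothing about that. A reader of the final report could take the per-protocol result as evidence that contamination had been dealt with, while the dilution of the intention-to-treat effect stayed where it was.

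**Working it through.** **1. Which meaning of visit is workable?**

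- *Research assessments.* Section 2.8 describes data collection at baseline and at follow-up, so two contacts. An enrolled participant with fewer than two would be one with no follow-up, and that is already the next exclusion in the list. This reading is largely redundant.
- *FCHV contacts.* This matches section 2.6 and Table 1, and the first home visits in Table 2. Controls on standard of care have no such contacts, so the threshold can select only within the intervention arm.

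The second is the only reading that gives the rule content of its own.

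**2. Do the exclusions reach control exposure?**

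| Exclusion (2.9) | Acts on | Concerns control exposure? |
|---|---|---|
| Too few visits | Intervention arm only | No |
| No follow-up assessment | Both arms | No |
| Ineligibility found after randomization | Both arms | No |

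The monitoring meant to detect spillover sits in the periodic reflections. Section 2.8 holds these with FCHVs and health workers from 12 to 24 purposively chosen facilities, all in the intervention arm. The article describes no measure of exposure on the control side.

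**3. Reference scale, from section 2.8.1.** Inputs: 51 clusters per arm, 35 participants per cluster, 60% uncontrolled, 10% loss, SD 17.75 mmHg, ICC 0.015, difference 3 mmHg. Two-sided alpha of 0.05 is my assumption.

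- Analysed per cluster: 35 × 0.6 × 0.9 = 18.9
- Design effect: 1 + (18.9 − 1) × 0.015 = 1.2685
- Effective n per arm: 51 × 18.9 / 1.2685 ≈ 760
- Standard error of the difference: 17.75 × √(2/760) ≈ 0.91 mmHg
- Power for 3 mmHg: 90.9%, against the stated 90%. The plan's figure reproduces.

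**4. How large could the selection bias be?** The documents give neither the share excluded nor its prognosis, so both are assumptions.

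*Simple form.* Let a share f of the intervention arm be excluded, with mean SBP higher by d for prognostic reasons. The full arm mean is m + f·d and the retained mean is m, so the estimate shifts by −f·d. With d = 5 mmHg: f = 0.2 gives 1.0 mmHg and f = 0.3 gives 1.5 mmHg.

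*Correlation form.* Let attendance and 12-month SBP have correlation ρ, with a true effect of zero. Dropping the lowest share f of attenders shifts the retained mean by ρ × 17.75 × φ(z_f) / (1 − f), where z_f is the normal quantile of f.

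| f dropped | Shift in mmHg, absolute ρ = 0.1 to 0.2 | Type I error (nominal 5%) |
|---|---|---|
| 10% | 0.35 to 0.69 | 7% to 12% |
| 20% | 0.62 to 1.24 | 10% to 26% |
| 30% | 0.88 to 1.76 | 15% to 43% |

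The two forms agree: at f = 0.2 the second implies d between 0.62/0.2 = 3.1 and 1.24/0.2 = 6.2 mmHg. The sign follows ρ. If low attenders have higher SBP, dropping them flatters the intervention; if they have lower SBP, the reverse.

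**5. What would unaddressed spillover cost?** If controls gain a share p of a 3 mmHg effect, the intention-to-treat difference is 3 × (1 − p). For p = 10%, 20% and 30% (assumed) it is 2.7, 2.4 and 2.1 mmHg, with power of 84%, 75% and 64%. None of the listed exclusions would change these figures.

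**The case against.** Much of the case on the other side stands. The primary analysis is intention-to-treat and is untouched by the exclusion rule; a supportive estimate is at stake. The plan does not rest its adherence analysis on exclusion alone, since the next sentence names probability weighting. The article never defines visits in that sentence, and a full analysis plan might do so. The mmHg figures come from chosen inputs and are not evidence that a bias of that size will occur.

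Several stronger readings are tempting, and the documents do not support them.

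- A reader might infer that the rule empties the control arm. Taken with complete literalness it would, but no analyst would apply it that way. The realistic result is one-sided trimming.
- A reader might infer that visit count is tied to prognosis by design, because home visits go to uncontrolled or poorly adherent patients. That follows cleanly only if visits means home visits. If group sessions count too, that passage mostly governs the mode of contact, not the number of contacts.
- A reader might infer that randomizing 102 facilities leaves no room for geographic buffering. Buffering could mean recruiting away from catchment borders; the article does not say what was done.
- A reader might infer that staff from both arms attend the social-network exchanges. Stratifying randomization by municipality (2.3) makes this plausible, but attendance by arm is not stated.

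Two things remain. The weighting is additional, so the one-sided exclusion still yields its own estimate. And section 3.1 assigns spillover to an analysis which, as section 2.9 defines it, has nothing to do with control exposure.

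**Conclusion.** The point holds in limited form. Applied as written, the visit threshold selects on post-randomization attendance in one arm only, and the per-protocol contrast then has a bias of unknown size and sign. This rests on reading visits as FCHV contacts, which is the only reading that does not largely duplicate another listed exclusion. The 0.35-1.76 mmHg range is an illustration that shows the bias need not be negligible beside a 3 mmHg target; it is not an estimate. To call the main trial result biased by this rule would be wrong.

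The spillover statement in section 3.1 does not follow from section 2.9 under any reading of visits. If spillover occurs, it may dilute the intention-to-treat effect, and the analysis named as remedy will not correct that. This is a correction worth making to a secondary analysis and to one claim in the limitations. It does not challenge the design.

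**What to change.** **Adherence analysis (2.9).** Remove the visit-count exclusion. Make the probability-weighting analysis already named there the adherence analysis. Define adherence as at least 2 FCHV sessions, group or home; weight adherent intervention participants by the inverse of their probability of adhering given baseline covariates; keep all controls. Process tracking already plans to record sessions and patients' participation in them, so the cost is mainly wording. The downside is that weighting removes bias only to the extent that measured baseline covariates explain attendance.

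A complier-average analysis with arm as instrument is a less safe substitute. It needs allocation to act only through attending two sessions, whereas facility training, coaching and the telemonitoring link can also reach patients who attend fewer.

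**Spillover (3.1).** Delete the statement that per-protocol analysis addresses it. Then do one of two things:

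- record attendance of control-facility staff at municipal meetings with CHPC content, and run a sensitivity analysis by that exposure; or
- report spillover as an unaddressed limitation that may dilute the intention-to-treat effect.

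The first costs an attendance column in meeting records. Section 2.5 places the study in the fourth quarter of its first year, so exposure before logging began may not be recoverable, and the report should say so. The trial status section states that no outcome data have been accessed, so both changes can still be made without knowledge of results.
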